### Timeline

Recruitment started September 23rd 2018 and was initially planned until the end of February 2020 with a follow-up until August 2020 (Table S1). Due to initial slow recruitment, we planned a prolongation of recruitment until June 2020 and of follow-up until December 2020. However, due to the SARS-CoV-2 pandemic, recruitment had to be paused on March 30th 2020, based on the recommendation of the National Institute for Medical Research, Tanzania. Until March 30th 2020, a total of 538 patients were included. To date, it is not possible to determine the date when recruitment will be resumed. Therefore, the study period will be prolonged again by the time that recruitment was paused.

### Recruitment

Patients are recruited in the emergency department, the outpatient clinics, and the wards of the St Francis Referral Hospital, Ifakara, and at the Chronic Disease Clinic Ifakara, and at the wards and outpatient clinics of the Mwanyamamala Regional Hospital, Dar es salaam, were tuberculosis patients were recruited for several other studies. All medical staff is regularly informed about the study, and posters with inclusion criteria and the phone number of the study team were distributed.

### Randomization

The randomization list was prepared in advance by the statistician, stratified by site (Ifakara and Mwananyamala) and HIV status (positive or negative) with randomly-varying block sizes. Patient allocation was done in a 1:1 ratio to the intervention or control group.

The sequence was concealed by using envelopes prepared by an independent person, based on the list prepared by the statistician. The envelopes are opaque and sealed, labelled only with the stratification information and a sequential number. Inside the envelope is a piece of paper confirming the stratification information and sequential number, and indicating the group allocation. The envelopes are stored securely. Checks are performed intermittently during enrolment to ensure that the randomization sequence is being respected.

Allocation of patients to the intervention or control group is done by the study clinical officers at each study site, after history taking, physical examination, collection of blood, urine and sputum for laboratory and microbiological examinations, chest X-ray, HIV testing, and informed consent. Based on the stratification of the patients (i.e site and HIV status), the study clinical officers take the next sequentially numbered envelope. They verify the information inside the envelope, and store the allocation paper in the patient file for source document verification if necessary.

### Sample size

Assumptions for the sample size calculation were based on data from the literature [1, 3, 6] and preliminary analysis of our observational study [9] (Table S2). Based on these assumptions, 73 and 85% of patients in the control and intervention groups, respectively, would be correctly managed. For a power of 95% with a two-sided alpha of 0.05, this yields a sample size of 592 patients. Assuming a lost to follow-up of 10%, 650 patients are required.

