**Methods:**

This open-label, parallel-group, superiority randomized controlled trial is done in a rural and an urban center in Tanzania. HIV-positive and -negative adults (≥18 years) with clinically suspected extrapulmonary tuberculosis are randomized in a 1:1 ratio to an intervention- or control group, stratified by center and HIV status. The intervention consists of a management algorithm including extended focused assessment of sonography for HIV and tuberculosis (eFASH) in combination with chest X-ray and microbiological tests. Treatment with anti-tuberculosis drugs is started, if eFASH is positive, chest X-ray suggests tuberculosis, or a microbiological result is positive for tuberculosis. Patients in the control group are managed according national guidelines. Treatment is started if microbiology is positive or empirically according to the treating physician. The primary outcome is the proportion of correctly managed patients at 6 months (i.e patients who were treated with anti-tuberculosis treatment and had definite or probable tuberculosis, and patients who were not treated with anti-tuberculosis treatment and did not have tuberculosis). Secondary outcomes are the proportion of symptom-free patients at two and 6 months, and time to death. The sample size is 650 patients.

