### Statistical analyses

Analyses and reporting will follow CONSORT guidelines (http://www.consort-statement.org/consort-2010) following intention to treat principles. Enrolment, randomisation and follow-up will be described using a flowchart. Baseline characteristics and outcomes will be described by group using frequencies and percentages for categorical variables and medians and interquartile ranges for continuous outcomes. The primary outcome will be compared between groups using logistic regression, reporting odds ratios with 95% confidence intervals. We will adjust for the stratification variables [23], and in sensitivity analyses for other baseline factors with imbalances between groups (by visual inspection, with no formal testing performed across groups) [24] or associated with missing primary outcome data [25]. We will assess effect modification of the primary outcome separately by HIV status and site, by using similar methods as for the primary outcome and an interaction between group and HIV status or site, respectively. Analyses of the categorical secondary and safety outcomes will follow similar methods as for the primary outcome, and with proportional hazards models for the time to death outcome if there are sufficient numbers of events. Inter-rater reliability of eFASH findings between the sonographer and the independent reviewer will be evaluated. A full statistical analysis plan will be developed.

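### The allowance for 10% loss to follow-up is slightly too small: 592 evaluable patients need 658 enrolled, and 650 covers about 9% loss, with negligible effect on power

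*Protocol article*

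**What the plan says.** All the figures stand in one paragraph, the Sample size section of the protocol article.

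- Assumed rates: "73 and 85% of patients in the control and intervention groups, respectively, would be correctly managed".
- Evaluable number: "For a power of 95% with a two-sided alpha of 0.05, this yields a sample size of 592 patients".
- Enrolled number: "Assuming a lost to follow-up of 10%, 650 patients are required".

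The Methods part of the abstract repeats the total: "The sample size is 650 patients". Allocation is 1:1 (Randomization section). The article does not name the sample-size formula or say how it went from 592 to 650. It refers to Table S2, which is not shown, for the assumptions behind the two rates.

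**The concern.** An allowance for loss to follow-up should leave the required number of patients after the stated fraction has gone, so the required number is divided by one minus the loss rate. The step from 592 to 650 does not do this. The total of 650 lies close to 592 × 1.1 = 651.2, which is what adding 10% on top would give.

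At stake is the consistency of a stated planning figure. The Discussion names loss to follow-up as a frequent challenge, especially in the rural setting, and offers the enlarged sample as the response. The loss that the sample can absorb should therefore be stated correctly. The article also says that a full statistical analysis plan is still to be developed, so the sentence may be carried over into that plan and into the trial report.

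**Working it through.** **Inputs** (all from the Sample size section, except the 1:1 allocation from Randomization): p1 = 0.73, p2 = 0.85, difference d = 0.12, two-sided alpha 0.05 (z = 1.960), power 95% (z = 1.645), 592 evaluable, 10% loss, 650 enrolled.

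**Step 1. Reproduce 592.** The pooled two-proportion formula without continuity correction, with mean rate 0.79, is

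n per arm = [1.960 × √(2 × 0.79 × 0.21) + 1.645 × √(0.73 × 0.27 + 0.85 × 0.15)]² / 0.12²

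= [1.960 × 0.5760 + 1.645 × 0.5697]² / 0.0144

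= (1.1290 + 0.9371)² / 0.0144 = 296.4

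The total is 592.9, or 594 if each arm is rounded up to 297. The stated 592 reproduces to within 2 patients, so the base figure is sound. For comparison, the unpooled formula gives 292.9 per arm, or 586 in total after rounding up.

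**Step 2. Apply the 10% loss.**

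| Calculation | Result |
|---|---|
| Enrolment needed to keep 592: 592 / (1 − 0.10) | 657.8, so 658 |
| Left from 650 after 10% loss: 650 × 0.90 | 585 |
| Shortfall in evaluable patients: 592 − 585 | 7 |
| Shortfall in enrolment: 658 − 650 | 8 (8/658 = 1.2%) |
| Largest loss at which 650 keeps 592: 1 − 592/650 | 8.9% |
| Adding 10% on top: 592 × 1.1 | 651.2 |

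**Step 3. Effect on power at 73% versus 85%.** With n per arm equal to half the evaluable total, the pooled test has

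power = Φ{[0.12 × √n − 1.960 × 0.5760] / 0.5697}

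- 592 evaluable (n = 296): Φ[(2.0646 − 1.1290) / 0.5697] = Φ(1.642) = 94.97%.
- 585 evaluable (n = 292.5): Φ[(2.0523 − 1.1290) / 0.5697] = Φ(1.621) = 94.7%.

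The loss is about 0.2 percentage points. By the unpooled formula, power at 585 is also 94.97%, and 585 is one patient below the 586 which that formula requires.

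**The case against.** The strongest case on the other side is that the gap is too small to matter. Power is stated as a whole percentage, and at 585 evaluable patients both the pooled (94.7%) and the unpooled (about 95.0%) calculations round to 95%. The assumed rates are also whole percentages, and that imprecision is far larger than the gap: moving either or both by half a point changes the evaluable number from 506 to 708. The 10% loss is itself a round planning value, and 650 covers 9% at the same precision. The inflation formula is not printed, so multiplication by 1.1 is only an inference, and 651.2 is not exactly 650.

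Most of this stands, and it fixes the size of the point. It does not remove the point. Uncertainty in the two rates affects how 592 arises, not whether 592 with 10% loss leads to 650. That step uses only printed numbers, so neither Table S2 nor a fuller protocol is needed to check it, and no other part of the article repairs it. How 650 came about remains an inference, but the inconsistency does not depend on it.

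Two stronger readings are tempting and should be resisted.

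- **That the trial misses its stated power.** A reader might infer this from 585 being below 592. The figures do not support it in any practical sense, because the loss is about 0.2 points and the result still rounds to 95%.
- **That the planned analysis makes the shortfall worse.** The Statistical analyses section says: "The primary outcome will be compared between groups using logistic regression, reporting odds ratios with 95% confidence intervals". Power on the log-odds scale is 94.1% at 585, and a reader might set that against 95%. On the same scale, however, 592 gives only 94.3%. Most of the distance from 95% therefore comes from changing the scale, not from the loss allowance, so the figure is not evidence for this point.

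**Conclusion.** The point holds as a minor arithmetic correction. Of the three printed figures (592 required, 10% loss, 650 enrolled), any two contradict the third. Enrolment is 8 patients (1.2%) below what 10% loss implies; equivalently, the evaluable number is 7 short. Nothing here shows an underpowered trial or calls for more recruitment.

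The inconsistency assumes only that 592 means patients with an evaluable primary outcome and that the 10% is a fraction of those enrolled, which is the ordinary reading of the sentence. The power figures assume 73% versus 85%, equal arms and an unadjusted two-proportion test. That is the method closest to the plan's 592, although the article does not name it.

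**What to change.** Keep enrolment at 650 and restate the sentence in one of two ways:

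- *A total of 650 patients allows for about 9% (8.9%) loss to follow-up while keeping 592 evaluable*; or
- *With 650 patients and 10% loss to follow-up, 585 are evaluable, giving about 94.7% power.*

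Use the same wording in the statistical analysis plan and the final report, and do not claim 10% loss and 592 evaluable together. The abstract can stay as it is, since it gives only the total. The cost is one sentence and a slightly less favourable stated figure. The recruitment target, the outcome and the analysis do not change.

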### Data collection and management

All data are managed using Epidata (http://www.epidata.dk/). Data are stored on a local computer. Data extraction is done daily and stored on a secured cloud storage service accessible only by study team members through a user name-password authentication. Since clinical, microbiological and sonographic findings are crucial for the decision to treat or not to treat a patient according to the protocol, these findings are accessible to the members of the study group. Information about results of microbiological data are given to the treating physicians of the patients in the control group. Direct access to source documents is permitted for purposes of monitoring and inspections. Only investigators and the monitoring team have access to the dataset. All data are checked and verified by the responsible investigators.

### Statistical analyses

Analyses and reporting will follow CONSORT guidelines (http://www.consort-statement.org/consort-2010) following intention to treat principles. Enrolment, randomisation and follow-up will be described using a flowchart. Baseline characteristics and outcomes will be described by group using frequencies and percentages for categorical variables and medians and interquartile ranges for continuous outcomes. The primary outcome will be compared between groups using logistic regression, reporting odds ratios with 95% confidence intervals. We will adjust for the stratification variables [23], and in sensitivity analyses for other baseline factors with imbalances between groups (by visual inspection, with no formal testing performed across groups) [24] or associated with missing primary outcome data [25]. We will assess effect modification of the primary outcome separately by HIV status and site, by using similar methods as for the primary outcome and an interaction between group and HIV status or site, respectively. Analyses of the categorical secondary and safety outcomes will follow similar methods as for the primary outcome, and with proportional hazards models for the time to death outcome if there are sufficient numbers of events. Inter-rater reliability of eFASH findings between the sonographer and the independent reviewer will be evaluated. A full statistical analysis plan will be developed.

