## Background

In resource-limited settings with a high tuberculosis prevalence, almost half of patients are treated empirically with anti-tuberculosis drugs upon clinical suspicion only [1–3]. Besides lack of available tests, this is mainly due to the poor sensitivity of microbiological tests, especially in patients co-infected with human immunodeficiency virus (HIV) or in those with suspected extrapulmonary tuberculosis [4, 5]. The decision to treat tuberculosis based on clinical signs and symptoms only has a low accuracy for culture-confirmed tuberculosis, and 30–60% of these decisions lead to false treatment [1, 3, 6]. The consequence is, that patients are unnecessarily exposed to potentially toxic drugs for long time periods, and the diagnosis of their real disease such as other infections, cancer or heart failure is delayed, or missed. Additional diagnostic methods are therefore needed to distinguish tuberculosis from other diseases with similar symptoms.

Ultrasound is a widely available diagnostic tool, which is used in various medical fields. Focused Assessment with Sonography for HIV and Tuberculosis (FASH) is a useful tool to detect signs of extrapulmonary tuberculosis, namely pleural and pericardial effusion, enlarged abdominal lymph nodes, hypoechogenic lesions in the spleen and the liver, ascites and thickening of the bowel wall [7]. FASH can be performed as a point of care bedside test and can be taught to personnel with little or no previous experience in ultrasonography [8]. In our observational study from rural Tanzania including 191 HIV-positive and -negative patients with suspected pulmonary or extrapulmonary tuberculosis, abnormal chest X-ray, presence of ≥1 FASH-sign, and elevated body temperature were independently associated with confirmed tuberculosis. A combination of ≥1 FASH sign, abnormal chest X-ray, and temperature ≥ 37.5 °C had a high (99.1%) sensitivity but a low (35.2%) specificity for confirmed tuberculosis. We concluded that ultrasound might be useful to exclude tuberculosis, in combination with other tests [9]. In a recent Cochrane metanalysis including HIV-positive adults, FASH signs predicted tuberculosis with a moderate diagnostic performance only. The authors also concluded that ultrasound results should be considered in combination with other tests, such as chest X-ray and Xpert MTB/RIF® only [10]. No randomized controlled trial evaluating sonography for the diagnosis of tuberculosis has been done yet.

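### The pre-specified primary model is valid but omits a plausibly strong baseline predictor, and extra covariates for the sensitivity analyses are chosen by visual imbalance rather than prognostic strength

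*Protocol article*

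**What the plan says.** In the protocol article, Statistical analyses, the primary outcome is compared by logistic regression, "reporting odds ratios with 95% confidence intervals". The model adjusts for the stratification variables, which Randomization gives as site and HIV status. Other covariates are added only "in sensitivity analyses for other baseline factors with imbalances between groups (by visual inspection, with no formal testing performed across groups"), or when they are related to missingness of the primary outcome. No candidate list or threshold for imbalance is given. Group percentages will be described, and a full SAP is promised.

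Randomization places allocation after "collection of blood, urine and sputum for laboratory and microbiological examinations, chest X-ray" and other baseline steps. Under Definitions, any positive microbiological test makes tuberculosis definite, and a treated patient with definite tuberculosis counts as correctly managed. Positive microbiology leads to treatment in the intervention group (Table 2) and in the control group (Abstract, Methods). Data collection and management adds that microbiology results reach the physicians treating control patients.

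Sample size is set in proportions: "73 and 85% of patients in the control and intervention groups, respectively, would be correctly managed".

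**The concern.** In a randomised trial the reason to adjust is that a covariate predicts the outcome. A rule that looks for imbalance can bring in a factor with no bearing on the outcome and leave out a strong predictor that happens to look even. Here the choice is made by eye, after the data by arm are available, in an open-label trial.

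A good candidate is already in the dataset. A patient whose pre-allocation sputum or urine is positive has definite tuberculosis by definition and should be treated in either arm. That patient is therefore likely to be correctly managed whatever the allocation. Such patients add variance to the comparison but carry little information about eFASH, and adjustment removes part of that variance.

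The effect measure is a second matter. The hypothesis and sample size concern proportions, but the only between-group estimate named is an odds ratio. With success rates of 73 to 85%, an odds ratio reads much larger than the change in proportions. It also moves when a prognostic covariate is added, so a primary and a sensitivity odds ratio can differ with nothing amiss. That makes the planned robustness check hard to read.

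**Working it through.** **Inputs from the protocol.** Rates of 73% and 85%; "For a power of 95% with a two-sided alpha of 0.05, this yields a sample size of 592 patients"; a total of 650 after an allowance for 10% loss; 1:1 allocation.

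**Assumed, because the protocol does not give it.** The share m of patients positive on pre-allocation sputum or urine, taken as 20 to 50%, and the proportion of positives correctly managed, taken as 100% or 95% in both arms.

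**1. The plan's own figure.** V = 0.73×0.27 + 0.85×0.15 = 0.1971 + 0.1275 = 0.3246.
- Unpooled: n per arm = V(1.960 + 1.645)²/0.12² = 293, total 586.
- Pooled: 297 per arm, total 594.
- Power at 296 per arm (592 in total) is 0.950.

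The stated 592 is reproduced. With 10% loss, 650 leaves 585 evaluable.

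**2. The same effect on three scales.**
- Difference: 0.85 − 0.73 = 12 points.
- Risk ratio: 0.85/0.73 = 1.16.
- Odds ratio: (0.85/0.15)/(0.73/0.27) = 5.667/2.704 = 2.10.

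**3. Upper bound on the precision gain (all positives correctly managed).** To keep the overall rates, the negatives must have c = (0.73 − m)/(1 − m) in controls and i = (0.85 − m)/(1 − m) in the intervention group. Variance ratio = (1 − m)[c(1 − c) + i(1 − i)]/0.3246.

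| m | c | i | ratio | reduction |
|---|---|---|---|---|
| 0.20 | 0.663 | 0.813 | 0.927 | 7% |
| 0.30 | 0.614 | 0.786 | 0.874 | 13% |
| 0.50 | 0.460 | 0.700 | 0.706 | 29% |

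The effect is zero in positives and 0.12/(1 − m) in negatives. Letting the sampled share of positives vary adds [m/(1 − m)]×0.0144/(2×0.3246) to the ratio. The reductions become 7%, 12% and 27%.

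Power at 585 is Φ(0.12/√(0.3246/292.5) − 1.960) = Φ(3.602 − 1.960) = 0.95. Dividing 3.602 by √0.927 gives 0.96, and by √0.706 gives 0.99.

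**4. A less favourable case (95% of positives correctly managed).** Logistic regression was simulated with N = 592 and 3,000 runs per scenario, with and without the binary covariate. Site and HIV status were not modelled.

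| m | power without | power with | OR without | OR with |
|---|---|---|---|---|
| 0.20 | 0.949 | 0.952 | 2.11 | 2.18 |
| 0.35 | 0.950 | 0.960 | 2.10 | 2.25 |
| 0.50 | 0.946 | 0.975 | 2.10 | 2.42 |

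The gain is about 0 to 3 points. Arm and covariate are independent here, so the movement in the odds ratio comes from conditioning and not from confounding.

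**5. Does either practice harm the test?** Under no effect, type I error was 0.042 to 0.053 without the covariate and 0.048 to 0.056 with it. It was 0.039 to 0.056 when adjustment was triggered by an imbalance above 5 points. Simulation standard error is √(0.05×0.95/3000) = 0.004. Reporting whichever of the two analyses looked better gave 0.061 to 0.068, but the protocol does not plan that.

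**The case against.** The strongest reply is that nothing in the primary analysis is wrong. Its covariates are fixed in advance and match the stratified randomisation, and the visual rule is confined to sensitivity analyses. The second selection route, association with a missing outcome, has a sound rationale. A covariate list can be left to the promised SAP. All of this stands, except that the article does more than leave the list open: it states a selection rule, and a SAP that followed it would inherit the rule.

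A reader might infer that visual selection biases the primary result or inflates its error rate. The documents do not support this: the rule does not touch the primary model, and the simulated error stayed at or below 0.056.

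A reader might also infer that X-ray and microbiology together largely determine the outcome. For microbiology the link follows from the definitions, but its reach depends on a positivity rate that is not given. Background describes microbiology as insensitive in this population, and sputum is tested only in those who can produce it, so the 50% scenario is the least supported. For X-ray the link is indirect. In the investigators' observational study abnormal X-ray was among the factors that "were independently associated with confirmed tuberculosis", but the outcome here is agreement between treatment and disease status, and X-ray is not part of the definition of definite tuberculosis.

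Nor will the difference in proportions be hidden, since percentages by group will be shown. What is not mentioned is a between-group difference with a confidence interval.

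Finally, sputum and urine are collected before allocation, but their results may come later. Because the specimen precedes allocation and the planned assays do not differ by arm, the result still serves as a baseline covariate. That does not extend to pleural, ascitic, cerebrospinal or lymph-node samples, which depend on later findings.

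**Conclusion.** The point holds as one of efficiency and interpretability, not validity. The primary model leaves out a plausibly strong baseline predictor already in hand, and the rule for further covariates targets imbalance rather than prognosis.

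The size is modest. The variance reduction is at most about 7 to 29% if 20 to 50% of patients are positive and all of them are correctly managed. The power gain is about 0 to 3 points from 95% if 95% of them are. Both rest on an assumed positivity rate and on comparison with a model without covariates; any overlap of positivity with site or HIV status would make the gain smaller. The sample size is unaffected.

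The mismatch of scale needs no such assumption: 12 points is a risk ratio of 1.16 and an odds ratio of 2.10. The change is worth making because it costs so little.

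**What to change.** Before analysis, in the SAP:

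- Pre-specify adjustment for any positive result (yes/no) from sputum or urine collected before randomisation, together with site and HIV status. Typical chest X-ray signs (yes/no) are optional. Exclude samples from other sites.
- Replace selection by visual imbalance with this named list. Keep the adjustment for factors associated with missing outcome data.
- Report a standardised adjusted risk difference with 95% CI beside the odds ratio.

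The cost is SAP wording and a short standardisation step, with no new data. There are two downsides. A few missing covariate values will need a stated handling rule; for example, the SAP must say how patients without sputum are classed. The positive stratum may also be close to 100% correctly managed, which calls for standardisation or a penalised fit.
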